### Participant-centred outcome measures

As well as feasibility outcomes, data on participant-centred outcome measures proposed to be used in the main trial will also be collected. We will do this using a range of techniques according to participants’ preference including, online, telephone and paper questionnaires. This will allow exploration as to which techniques for data collection are most acceptable and feasible.

The timing and sequence of all assessments are summarised in the SPIRIT figure (Fig. 4). All study participants will complete follow-up assessments at 2 and 4 months post-randomisation. At the 4-month data collection point, all the outcomes that were assessed at baseline will be reassessed. In addition, at 4-month follow-up, resource use will be collated by maternal self-report.

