### Perinatal emotional skills groups

Perinatal Emotional Skills Groups (ESGs) will be delivered as specified in the Maternal Emotional Wellbeing manual [31]. An uncontrolled evaluation of ESGs in a cohort of 21 women, found that there was strong evidence of a reduction in mental distress over the intervention period (Cohen’s *d* = 0.83; *p <* .001) and at the end of treatment, women reported substantial improvements in their ability to manage difficult emotions [31]. The intervention comprises up to 2 individual preparatory sessions, followed by 12 group sessions. The individual sessions last up to 90 min and subsequent group sessions last up to 2 h. Participants receiving ESGs will also continue to be cared for as usual by their perinatal mental health team.

The over-arching content of perinatal ESGs is displayed in Fig. 2 and the details of each module are displayed in Fig. 3. Groups usually treat up to 6 women and the groups are organised into four modules on emotion regulation, distress tolerance, mindfulness and interpersonal effectiveness (Fig. 2). These modules are focused on the acquisition of emotional skills and each session is supplemented with “Keeping Baby in Mind” teaching skills relevant to becoming a parent of a new child; these skills can be taught and practiced both prenatally, as well as postnatally. The groups will be run by a clinical psychologist working with a trained nurse or other qualified perinatal clinician.

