### Outcomes

#### Feasibility outcomes

The main aim of this study is to demonstrate the feasibility of conducting a trial to evaluate the intervention, including the feasibility and acceptability of randomising the intervention during the perinatal period and the feasibility of outcome measure collection.

Feasibility of recruitment will be assessed by exploring:The appropriateness of the eligibility criteria, as measured by the number of those referred to the trial over the study period, who meet the eligibility criteria.The success of recruitment, as measured by the number of eligible patients who consent to participate in the trial over the study period, and the number of patients who decline to participate.Retention rates, as measured by the number of participants who consent to participate that remain in the trial by 4-month follow-up.

Feasibility of the assessment battery will be assessed by measuring:The number/proportion of participants with complete baseline data over the study periodThe number/proportion of participants with complete follow-up data at 4 months follow-up.

Feasibility of the intervention will be assessed by measuring:The number/proportion of participants attending all 12 sessions of treatment during the treatment phase of the studyThe number/proportion of participants attending at least 9 sessions of treatment during the treatment phase of the studyThe number/proportion of participants retained at the end of each module of treatment.

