### Sample size

In keeping with recommendations for feasibility studies [32], we have not based plans for sample size on a power calculation. A pragmatic sample size of 48 will allow us to estimate, with a desirable degree of precision, the rate of recruitment and retention in a future phase III trial. In 2018, in the selected catchment areas covered by Bristol and London, there were a total of 24,697 live births (www.ons.gov.uk). Assuming a community prevalence of BPD of 2% [33], across the 2 centres, 494 women with BPD could have been eligible for recruitment. Our recruitment target of 48 women from a pool of 494 (9.7%) is a low recruitment target, but we have been cautious as people diagnosed with BPD can be harder to recruit to studies [34]. Notwithstanding, our collaborators in perinatal services, the third sector and our advisors with lived experience of personality disorder have all encouraged us to undertake this study. We therefore think that there will be significant interest in the research and that the recruitment rate will be higher. Assuming a conservative recruitment estimate of 9.7%, a sample size of 48, will give us a 95% confidence interval for recruitment of between 7.3% and 12.7%. The trial aims to recruit 48 participants over 12 months from 2 perinatal mental health services at 2 trial centres, with a target of approximately 4 participants randomised per month.

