### Assignment of interventions

After consenting to participation and completing screening assessments, eligible individuals will be randomly allocated, on a 1:1 ratio, to either ESGs + TAU or to TAU. The randomisation sequence will be generated by the Research Electronic Data Capture Service (REDCap) at the University of Bristol (https://brtcclinical.bris.ac.uk/redcap/). Randomisation will be stratified by centre. Appropriate staff at all sites, as delegated by the PI, will be provided with log-in details for the secure online randomisation system. Throughout the study, the randomisation list will be encrypted and held with the Trial Coordinating Office to ensure that the study researchers remain blinded to treatment allocation. At the end of the study, the randomisation list will be unencrypted and placed in the Trial Master File.

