### Adverse events

All adverse events will be assessed for seriousness, causality and expectedness by the Principal Investigator and will be recorded and reported from the point of randomisation until the 4-month follow-up assessment or the point of withdrawal from the study. Hospitalisations for elective treatment of a pre-existing condition will not be reported as serious adverse events.

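### Outcome and adverse-event windows close 4 months after individual randomisation, but at about one ESG allocation per centre per month women may wait for a group and still be in therapy then

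*Protocol article*

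**What the plan says.** **Accrual and allocation.** The Sample size section plans 48 women over 12 months at 2 centres, "with a target of approximately 4 participants randomised per month". Under Assignment of interventions, "eligible individuals will be randomly allocated, on a 1:1 ratio, to either ESGs + TAU or to TAU", and "Randomisation will be stratified by centre".

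**Treatment.** The section on perinatal emotional skills groups describes up to 2 individual preparatory sessions and then 12 group sessions. On size it says: "Groups usually treat up to 6 women". It gives no session frequency, minimum group size or rule on open or closed entry. It does not say whether the two centres share groups.

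**Clock.** Under Participant-centred outcome measures, "All study participants will complete follow-up assessments at 2 and 4 months post-randomisation". The Discussion confirms that follow-up ends at 4 months. Under Adverse events, recording runs from randomisation "until the 4-month follow-up assessment or the point of withdrawal from the study".

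**Attendance.** The feasibility outcomes count women attending all 12 sessions, women attending at least 9, and "participants retained at the end of each module of treatment". These counts refer to the treatment phase, not to month 4. Data analysis defines completing the intervention as nine or more of the 12 sessions.

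**The concern.** A group treatment starts when there is a group, whereas every assessment is dated from one woman's randomisation. No section of the article links the two. If groups take time to fill, some ESG women reach the 4-month assessment part-way through the course, or before it has begun.

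Two things are at stake:

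- **The 4-month difference in means.** It would still be a valid comparison as randomised. But it would average over waiting, part-treated and fully treated women in unknown proportions, and nobody planning the definitive trial could tell how much treatment it reflects.
- **Adverse events.** Those arising in sessions after month 4 fall outside the stated window. They would go unrecorded in the arm where the intervention's harms would show.

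**Working it through.** **1. The plan's rate.** 48 / 12 = 4.0 randomised per month, as stated. Divided over 2 centres and 2 arms, 4 / 2 / 2 = 1.0 ESG allocation per centre per month (2.0 if the centres share groups). That is 12 ESG women per centre over the year.

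**2. The clock.** 4 months = 17.4 weeks, at 4.348 weeks per month.

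**3. Assumptions not in the article.** Weekly sessions; closed groups of trial participants only; preparation of *p* = 0 or 2 weeks after the group has formed; random (Poisson) arrivals. The first session is held on the start day, so session 12 comes 11 weeks later and session 9 comes 8 weeks later.

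**4. Evenly spaced illustration.** In a single-site group of six, successive members wait 5, 4, 3, 2, 1 and 0 months. With *p* = 0, the weeks left between group start and each woman's own 4-month point are −4.3, 0.0, 4.3, 8.7, 13.0 and 17.4. Counting one session per completed week gives 0, 0, 4, 8, 12 and 12 sessions. Counting one on the start day gives 0, 1, 5, 9, 12 and 12.

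**5. Random arrivals.** A woman with *k* later members in her group waits a Gamma(*k*, rate) time. For group size *g*,

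share = (1/*g*) × Σ (*k* = 0 to *g* − 1) P(wait ≤ slack),

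where slack is 17.4 − *p* − 11 weeks for all 12 sessions, 17.4 − *p* − 8 for nine, and 17.4 − *p* for having started.

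Worked case: single-site group of six, *p* = 0, all 12 sessions. Slack = 6.4 weeks = 1.47 months. The probabilities for *k* = 0 to 5 are 1, 0.770, 0.432, 0.184, 0.062 and 0.017. Their sum is 2.465, and 2.465 / 6 = 0.41.

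In each range below, the less favourable figure is for *p* = 2 and the more favourable for *p* = 0:

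| Closed weekly groups | Offered all 12 by month 4 | Offered 9 by month 4 | Not started by month 4 |
|---|---|---|---|
| Single site, 6 | 33–41% | 45–52% | 23–29% |
| Single site, 4 | 50–60% | 64–72% | 9–12% |
| Pooled, 6 | 50–64% | 70–80% | 3–5% |
| Pooled, 4 | 70–83% | 87–93% | under 1% |

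Taking complements of the first column, 17–67% would still be owed sessions at month 4.

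**6. Sensitivity to frequency.** With evenly spaced arrivals and twice-weekly sessions, 3 of 6 in a single-site group of six could have all 12 by month 4. With fortnightly sessions nobody could, even with no wait: 11 × 2 = 22 weeks from first to last session exceeds 17.4.

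**The case against.** The strongest reply is that the problem depends on arrangements the article never states. Six is a ceiling with no minimum. With evenly spaced weekly arrivals, a single-site pair or a pooled group of three would finish in time or within about a session of it. Online delivery is allowed, and women are shown how to log on to a therapy platform, so sharing groups across centres is plausible. Each team first lists its potential participants, which could bring early arrivals closer together. The module-retention outcome fits entry at the start of any module as well as a single closed course. The full protocol, the flow chart and the assessment schedule are not shown and may settle the scheduling.

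All of this stands, and it rules out some stronger readings that a reader might infer:

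- **That groups cannot form or cannot deliver 12 sessions in time.** The article does not support this. The table shows large shares offered the full course under several formats, and rolling entry would largely remove the problem.
- **That the completion figures are cut off at month 4.** They are not, because attendance is counted over the treatment phase.
- **That the trial's go/no-go decision is compromised through the diluted contrast.** The progression criteria are recruitment, uptake and 4-month follow-up. The contrast is reported with confidence intervals only, without hypothesis tests.

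What the reply does not remove is that the accrual rate, the clock starting at individual randomisation and the adverse-event cut-off are all printed, and they fit a 12-session group course only under conditions left unsaid.

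**Conclusion.** The point holds in conditional form. At about one ESG allocation per centre per month, women may wait for a group while windows that close at 4 months are already running. With closed weekly groups of four to six trial participants and 0 to 2 weeks' preparation, between about a sixth and two thirds of ESG women would still be owed sessions at month 4. Judged against the nine-session definition of completion, the shortfall is smaller: 7–13% in pooled groups of four and 48–55% in single-site groups of six. A substantial share not yet started arises mainly with single-site groups of six; with pooled groups it is at most about 5%.

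These figures rest on unstated frequency, entry and pooling arrangements, so they give a range of exposure and not a forecast. The firm part is that, followed as written, the plan would not record adverse events in any sessions after month 4. Nor does the article plan to report how much treatment had been available when outcomes were measured.

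**What to change.** 1. **Adverse events.** Continue recording to the last ESG session for women still in therapy after month 4. Report those later events separately, so that the between-arm comparison keeps its common 4-month window.
2. **Feasibility outcomes.** Add the interval from randomisation to first group session, and the number of sessions offered by the 2-month and 4-month assessments. Report the 4-month differences in means alongside them.
3. **Group start.** Reconcile the group-start arrangement, whether rolling entry, pooling of centres or another, with the 4-month clock. If rolling entry is intended, stating it would answer most of this point.

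The cost is slightly more data collection and an adverse-event window that is longer in one arm, which the separate reporting handles.

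Batched randomisation against a set group start is an option to consider for the definitive trial, not a required change here. To fill a group of six at 1:1, a centre needs 12 consented women. At 2 per month the first would wait (12 − 1) / 2 = 5.5 months and the average woman 2.75 months, in both arms, while eligibility ends 12 months after birth.

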**Fig. 4 Fig4:**
[figure not shown]
SPIRIT figure

### Nested qualitative study

A qualitative study will be nested within the feasibility trial to help provide insight into participants’ and therapists’ experiences of the trial and the intervention. This will provide further information about the feasibility and acceptability of the intervention and future definitive trial design. After the completion of treatment, purposive samples of patients and staff will be invited to participate in a qualitative interview. All interviews will use a topic guide, will be audio-recorded using an digital recorder, and will be fully transcribed and analysed thematically. Consenting participants will be offered a £20 voucher to reimburse their time and effort for attending the qualitative interviews. The following groups will be interviewed:Participants in the intervention and standard care arms.

These will be conducted at the completion of treatment with a purposive sample of between 10 and 15 participants. Maximum variation sampling will ensure that, where possible, women from different socioeconomic status, ethnicity and different levels of attendance at the intervention are selected. We will reflect upon sample requirements as data collection progresses. Questions will include views on the recruitment process, including screening and randomisation; motivation for joining the study; women in the intervention arm will be asked about aspects of the intervention they found most helpful and most challenging and all women will be asked about their experience of usual care; content and format of ESG sessions (e.g. length, online delivery); and feedback on the appropriateness of the measures being used, including burden of completion and preferred methods of administration.2)Study decliners and participants who drop out of treatment

We will seek the views of up to 10 eligible women who, at some stage in the recruitment process, decide to decline participation or the views of participants who withdrew partway through. Interviews with these women will also allow us to explore their views about standard care. It is likely that participants who decline or drop out will be less willing to talk to the researchers, but we will attempt to capture their views, assuming they are willing to give consent. Questions will include reasons for declining or dropping out and whether their continuing participation in the study could have been better supported.3)Staff interviews

Interviews with all practitioners and their supervisors will be carried out at the end of the intervention. These will focus on the ease of delivery, the value of training and supervision, as well as the acceptability, strengths and weaknesses of the intervention and the research process. The staff interviews will also seek staff insights into the feasibility of rolling online ESGs out more widely across the NHS, including their views about the training and funding required to support this activity.

### Sample size

In keeping with recommendations for feasibility studies [32], we have not based plans for sample size on a power calculation. A pragmatic sample size of 48 will allow us to estimate, with a desirable degree of precision, the rate of recruitment and retention in a future phase III trial. In 2018, in the selected catchment areas covered by Bristol and London, there were a total of 24,697 live births (www.ons.gov.uk). Assuming a community prevalence of BPD of 2% [33], across the 2 centres, 494 women with BPD could have been eligible for recruitment. Our recruitment target of 48 women from a pool of 494 (9.7%) is a low recruitment target, but we have been cautious as people diagnosed with BPD can be harder to recruit to studies [34]. Notwithstanding, our collaborators in perinatal services, the third sector and our advisors with lived experience of personality disorder have all encouraged us to undertake this study. We therefore think that there will be significant interest in the research and that the recruitment rate will be higher. Assuming a conservative recruitment estimate of 9.7%, a sample size of 48, will give us a 95% confidence interval for recruitment of between 7.3% and 12.7%. The trial aims to recruit 48 participants over 12 months from 2 perinatal mental health services at 2 trial centres, with a target of approximately 4 participants randomised per month.

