### Participant eligibility, screening and consenting

Figure 1 outlines the key phases of the trial. We will first identify a key clinical contact in each participating team who will be asked to provide a list of all potential participants who meet the following inclusion criteria:At least 18 years oldLikely to have a diagnosis of BPDEither pregnant (from week 15 gestation onwards) or are within 12 months of having a live birth.

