### Screening assessment of potential participants

The researcher will first briefly explain the study, check that a PIS has been received and answer any questions the participant may have. With verbal consent, the researcher will then proceed with the screening assessment which will consist of three elements:We will use the self-report Standardised Assessment of Personality Abbreviated Scale (SAPAS) [19] to check that potential participants have probable personality disorder. The SAPAS is a reliable, valid and acceptable scale for assessing personality-related difficulties. A score of three or more on the SAPAS correctly identifies 90% of people with DSM-IV personality disorder and has a sensitivity 0.94 and specificity 0.85 [19]. To be included in the study a potential participant will need to score 3 or more on the SAPAS.The researcher will also complete a 15-item BPD checklist with the patient (which has been used in the UK Adult Psychiatric Morbidity Survey [20]), confirming the presence or absence of DSM symptoms of BPD. In keeping with international diagnostic guidelines [1], patients will need to positively endorse at least 5/9 of the symptom domains covered by the 15 items to be eligible for the trial.The researcher will check whether the patient would be willing and able to receive emotional skills groups (face-to-face or online) if they were randomised to this.

If a woman meets the screening criteria, they will be offered a baseline assessment with the researcher. Those who are ineligible will be thanked for their time and informed of the reason(s) for this. Following the eligibility check and prior to commencing the baseline assessment, the researcher will obtain the written consent of all eligible women relating to their participation in the trial. The researcher will answer any further questions the individual may have, and re-check whether they are still willing and able to receive emotional skills groups if they were randomised to this. Consent will be obtained either via an online ‘e-consent’ method (if the baseline assessment is being conducted remotely) or via paper-based informed consent, if the researcher is meeting with the individual face-to-face. Individuals attending a face-to-face appointment will be given a copy of their written consent form to keep. Individuals completing the assessment remotely will receive an electronic copy of their e-consent form via email. A copy will also be sent to the patient’s GP.

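### The stated recruitment interval of 7.3% to 12.7% is computed on a projected pool of 494 women that no planned feasibility proportion uses, so it does not support the precision claimed for recruitment and retention

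*Protocol article*

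**What the plan says.** The Sample size section describes 48 as a pragmatic number, not based on a power calculation. It says that this number "will allow us to estimate, with a desirable degree of precision, the rate of recruitment and retention" in a future trial. The supporting figures start from 2018, when "there were a total of 24,697 live births" in the selected catchment areas. With an assumed community prevalence of 2%, the section concludes that "across the 2 centres, 494 women with BPD could have been eligible for recruitment". The target of 48 is then expressed as 9.7% of that pool, and the section states that "a sample size of 48, will give us a 95% confidence interval for recruitment of between 7.3% and 12.7" per cent. This is the only interval in the section. None is given for retention.

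Elsewhere the rates to be reported are defined differently. Women are found through lists from clinical contacts in the participating perinatal teams, then approached by clinicians and screened. Under Feasibility outcomes, recruitment success is measured by "the number of eligible patients who consent to participate in the trial over the study period", together with the number who decline, and retention is counted among those who consent. Data analysis plans proportions with 95% intervals for consent, baseline completion and randomisation, intervention completion (at least 9 of 12 sessions) and follow-up. Progression criteria asks for at least 36 recruited, uptake by at least 75% of the active arm, and 4-month follow-up by 75% of the target sample.

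**The concern.** The sentence credits a sample of 48 with a precision of under 3 percentage points. An interval that narrow needs a denominator of several hundred, and the only such number in the section is the projected 494. Those women are a product of a birth count and an assumed prevalence. They are not a sample that the trial will observe.

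The stated purpose of the sample size is to estimate recruitment and retention for planning the definitive trial. If its only quantitative support describes neither the consent rate nor the retention rate, a reader of the protocol has no basis for judging how well 48 women will serve that purpose, or how firmly a result near a 75% progression threshold can be read.

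**Working it through.** **Inputs.** From Sample size: 24,697 births, 2% prevalence, target 48, stated interval 7.3% to 12.7%. From Assignment of interventions: 1:1 allocation, hence 48/2 = 24 in the active arm. From Progression criteria: at least 36 recruited, and 75% for uptake and for follow-up.

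**Formula.** Exact (Clopper-Pearson) 95% interval for x out of n: the lower limit is the 2.5% quantile of Beta(x, n − x + 1); the upper limit is the 97.5% quantile of Beta(x + 1, n − x).

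**Step 1: reproduce the stated figure.** 24,697 × 0.02 = 493.9, rounded to 494. 48/494 = 9.72%. The exact interval is 7.25% to 12.68%, which is the printed 7.3% to 12.7%. Other methods on 48/494 come close without matching both limits (Wilson 7.41% to 12.65%; Wald 7.10% to 12.33%). The half-width is (12.68 − 7.25)/2 = 2.7 points, with n = 494.

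**Step 2: see what the 494 depends on.** The binomial interval treats 494 as a known sample size. It moves directly with the prevalence; the alternatives to 2% below are my assumptions.

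| Prevalence | Pool | 48/pool | Exact 95% CI |
|---|---|---|---|
| 1% | 247 | 19.4% | 14.7% to 24.9% |
| 2% (protocol) | 494 | 9.7% | 7.3% to 12.7% |
| 3% | 741 | 6.5% | 4.8% to 8.5% |

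Changing the prevalence by one point in either direction moves the estimate outside the stated interval, so the interval leaves out the main source of uncertainty in this ratio.

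**Step 3: match the denominator to the planned proportions.** Eligibility is assessed among women referred, consent among eligible women, intervention completion in the active arm, and retention among those who consented. None of these denominators is 494.

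**Step 4: precision on denominators the trial will have.**

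| Rate | x/n | Exact 95% CI | Half-width |
|---|---|---|---|
| 4-month follow-up, full sample | 36/48 = 75% | 60.4% to 86.4% | 13 points |
| 4-month follow-up, 36 recruited | 27/36 = 75% | 57.8% to 87.9% | 15 points |
| Skills-group uptake or completion | 18/24 = 75% | 53.3% to 90.2% | 18 points |

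The 27/36 row shows only the width with a smaller sample. The progression criterion refers to the target sample, so 27 women followed up would not meet it.

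The number of eligible women approached is not given. As a range of assumptions:

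| Eligible women approached (assumed) | Consent | Exact 95% CI | Half-width |
|---|---|---|---|
| 60 | 80% | 67.7% to 89.2% | 11 points |
| 96 | 50% | 39.6% to 60.4% | 10 points |
| 160 | 30% | 23.0% to 37.7% | 7 points |
| 240 | 20% | 15.1% to 25.6% | 5 points |

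**The case against.** The strongest reply is that nothing is miscalculated and little hangs on the sentence. The interval reproduces exactly. The sample size is openly pragmatic, and 494 is a fair rough check that the catchment can supply 48 women. The interval is attached to recruitment alone, at an openly assumed rate, and feeds no decision rule, because recruitment progresses on a count of 36. Data analysis already plans 95% intervals for the real feasibility proportions, so the results paper will show the true uncertainty. A condensed article may also leave the precision for retention to the full protocol.

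Most of this stands, and it limits the point to the sample-size rationale. It does not rescue the sentence. The section makes an explicit claim of precision for recruitment and retention, and the one figure offered in support belongs to a ratio that the trial does not plan to report. That is a fault in what is written, whatever the full protocol adds.

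A reader might also infer that recruitment is capped at 48, so that 48/494 is fixed by design and estimates nothing. The documents do not support that. They call 48 a target and an aim, set a criterion at 36 and foresee stopping for poor recruitment. The number recruited can vary, and with 36 women the ratio would be 36/494 = 7.3%.

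**Conclusion.** The point holds as a fault in the sample-size rationale that should be fixed. The interval of 7.3% to 12.7% is correct for 48/494, but 494 is a projection and the denominator of no planned proportion, and 9.7% is the target restated against it. The claim of good precision for recruitment and retention is therefore unsupported as written. On observed denominators the half-width is about 13 points for follow-up (n = 48) and about 18 points for skills-group uptake or completion (n = 24), against the 2.7 points stated for recruitment. These figures assume that the observed rates equal the 75% thresholds and that the arms are equal.

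Three stronger readings are not supported:

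- That the rates driving progression include consent. Consent is not a progression criterion, and its half-width of about 5 to 11 points rests on assumed denominators.
- That the correct interval would be 9.7% on a sample of 48. Women already recruited are not the denominator of a recruitment rate.
- That 494 should be replaced by a larger pool because the eligibility window ("pregnant (from week 15 gestation onwards) or are within 12 months of having a live birth") covers more than one year of births. A larger births-based pool would be just as unobserved, and it would only strengthen the catchment check.

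**What to change.** In the Sample size section, keep the 494 solely as a rough check of catchment size and delete the interval based on it. In its place, state the expected exact 95% intervals on the denominators the trial will observe:

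- 4-month follow-up: 36/48, 60% to 86%; if only 36 are recruited, 27/36, 58% to 88%.
- Skills-group uptake or completion in the active arm: 18/24, 53% to 90%.
- Consent among eligible women approached, as a range over stated assumptions: for example 48/60, 68% to 89%; 48/96, 40% to 60%; 48/240, 15% to 26%.

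Add a sentence to Progression criteria saying that the 75% thresholds will be read with these widths in mind: an observed 75% is compatible with true rates down to about 60% for follow-up and 53% for uptake.

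The cost is a less favourable stated precision. The sample size, outcomes, analyses and progression thresholds are unchanged, and no extra participants are needed.
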